#### Qualitative phase

The qualitative phase of our study will draw on the principles of qualitative description methodology. This approach is suitable for mixed method study to address clinical questions. This approach is well suited here as this approach will enable us to gain perspectives from participants to understand and describe the phenomenon in terms of literal descriptions and dwell on practical relevance of the information for health care users [27].

We will employ a combination of purposeful sampling techniques, including criterion-based, maximum variation, and snowballing sampling techniques, to seek an equally representative sample in terms of the HIV stakeholders groups (policy, research, practice) and across all WHO geographical regions (African Region, Region of the Americas, South-East Asia Region, European Region, Eastern Mediterranean Region, and Western Pacific Region) [28].

Based on sample size recommendations to reach theoretical sampling, we anticipate performing 25–30 interviews, with 4–5 from each representative group. This sample size seems appropriate to capture information-rich data. This estimation of interview participants is based on a study involving key stakeholders’ perspectives and experiences on defining and identifying health research gaps [26].

#### Quantitative phase

We will disseminate the surveys to the pre-defined HIV stakeholders groups. We will use the email listservs of organizations working in HIV care, such as the Ontario HIV Treatment Network (OHTN), World Health Organization (WHO) and Joint United Nations Programme on HIV/AIDS (UNAIDS), Global Fund, International AIDS Society (IAS), Kaiser Family Foundation (KFF), The United States President’s Emergency Plan for AIDS (PEPFAR), Canadian Foundation for AIDS Research (CANFAR) and regional WHO groups. Researchers will be identified from publications on retention in care in the CASCADE database (a database of randomized trials on the HIV care cascade) [29]. We will also reach out to existing collaborations and professional associations such as the International AIDS Society (IAS), the Canadian Association for HIV Research (CAHR), and the International Association of Providers of AIDS Care (IAPAC).

To further supplement the recruitment process, we will publicize our study on social media platforms like Twitter and LinkedIn. Patients will be recruited and identified from online patient support groups and organizations serving those patients, such as REALIZE, POZ Community Forum [28]. We will submit an amendment to HiREB regarding any changes in recruitment methods based on guidance of the organizations.

We will disseminate the survey online in the stakeholders’ groups. If response rates are lower than our calculated sample size, we will use a snowballing approach to include responses from participants interested in this topic [30].

We will use a proportional quota sampling method to achieve a diverse and representative sample of participants. We will divide the sample into our pre-defined three strata (policy, health research, and practice) so every HIV stakeholder group is equally represented [31]. People who belong to more than one group will be asked to declare the group they primarily identify with. We will obtain a pre-determined sample population of 385 based on the formula for proportions for a survey, which is the maximum sample size required to estimate a population proportion of 50% with a 95% level of confidence and a 0.5% margin of error. These computations are performed with WINPEPI [32].

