**Methods:**

We will use an exploratory sequential mixed methods design involving HIV stakeholder groups such as people living with HIV, people involved in providing care for PLHIV, and people involved in decision-making about PLHIV. In the qualitative phase of the study, we will conduct 20–25 in-depth interviews to collect the perspectives of HIV stakeholders on using their preferred retention measures. The findings from the qualitative phase will inform the development of survey items for the quantitative phase. Survey participants (n = 385) will be invited to rate the importance of each approach to measuring retention on a seven-point Likert scale. We will merge the qualitative and quantitative findings phase findings to inform a consensus-building framework for a standard definition of retention in care.

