### Quantitative phase

We will compute the mean (standard deviation) or frequency (percent) based on the survey responses as appropriate for the data.

To determine the level of importance that participants allocate to each item we will compute the mean (SD) or median (quartiles). Only items with a mean of 4 or more out of seven will be considered as important. The mean will inform us which approaches to measuring retention are preferred by the participants. Results will be aggregated by stakeholder groups.

The results will be analyzed using IBM SPSS statistical software [38]. An outline of the study is shown in Fig 1.

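### The survey size of 385 is justified by a 0.5% margin of error, but 385 is the answer for a 5% margin, so the stated precision is overstated tenfold

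*Protocol article*

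**What the plan says.** The sample size for the survey is given in the protocol article under Sampling and sample size, Quantitative phase: "We will obtain a pre-determined sample population of 385 based on the formula for proportions for a survey". The same sentence describes this as the largest number needed to "estimate a population proportion of 50% with a 95% level of confidence and a 0.5% margin of error". WINPEPI is named as the software.

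The abstract repeats the number: "Survey participants (n = 385) will be invited to rate the importance". No other section gives a margin of error. The article states no finite population size, design effect or allowance for non-response.

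Two further parts of the plan bear on how the margin can be read:

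- **Sampling.** Respondents are to be reached through organisational mailing lists, professional associations, patient groups and social media. Quotas apply in three stakeholder strata, and snowballing is added if responses fall short.
- **Analysis.** Items are rated on a 7-point Likert scale and summarised by means or medians. An item counts as important if its mean is at least 4. On reporting, the plan says: "Results will be aggregated by stakeholder groups".

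**The concern.** The number 385 is the familiar answer for a proportion of 50%, 95% confidence and a margin of 5 percentage points. Printed beside a margin of 0.5%, it cannot be right: the required sample size varies with the inverse square of the margin, so a tenfold smaller margin needs a hundredfold larger sample.

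This sentence is the whole justification for the size of the quantitative phase and its only statement of precision. As printed, the margin and the sample size contradict each other. A reader who accepts the margin will think that percentages from the survey are known ten times more precisely than they would be. A reader who repeats the calculation has to work out which of the two numbers is the slip.

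**Working it through.** **Inputs**, all from the sample size sentence:

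- proportion p = 0.50
- confidence 95%, two-sided, so z = 1.96 (unrounded 1.959964; z² = 3.841459)
- stated margin d = 0.005
- stated n = 385

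**Step 1: try to reproduce the stated figure from the stated inputs.**

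n = z² p(1 − p) / d² = 3.841459 × 0.25 / 0.005² = 0.960365 / 0.000025 = 38,414.6, rounded up to 38,415.

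The stated 385 is not reproduced. The ratio is 38,415 / 385 = 99.8.

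**Step 2: see whether another reading of a 0.5% margin gives 385.**

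| Reading of the 0.5% margin | n required |
|---|---|
| Two-sided 95%, half-width 0.5 points | 38,415 |
| One-sided 95% | 27,056 |
| Continuity-corrected interval | 38,615 |
| Wilson interval | 38,411 |
| 0.5% as full width (half-width 0.25 points) | 153,659 |

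None comes near 385. A finite population correction, n = n₀ / (1 + (n₀ − 1)/N) with n₀ = 38,414.6, gives 385.1 when N = 389. The whole target population would have to be about 389 people. That does not fit a survey of stakeholders recruited globally, and the article states no population size.

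**Step 3: use a 5% margin.**

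n = 0.960365 / 0.05² = 0.960365 / 0.0025 = 384.15, rounded up to 385.

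This matches the stated figure exactly. The 5% must be the half-width: read as a full width (d = 0.025) it would give 1,537.

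**Step 4: find what 385 respondents deliver.**

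Half-width = z × √(p(1 − p)/n) = 1.959964 × √(0.25/385) = 1.959964 × 0.025482 = 0.04994, or ±4.99 percentage points.

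Against the stated margin: 4.99 / 0.5 = 9.99, about tenfold. Seen the other way, an interval of ±0.5 points around a proportion of 50% from 385 respondents has z = 0.005 / 0.025482 = 0.196, which corresponds to about 16% confidence and not 95%.

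**Step 5: illustrate one stakeholder group (assumption: three groups filled equally).**

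385 / 3 = 128.3, so about 128 per group. Half-width = 1.959964 × √(0.25/128) = 0.0866, or ±8.7 percentage points.

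**The case against.** The strongest reply is that this is a misprint without consequence. An exact match at 5% suggests that the calculation was done correctly and that 5% or 0.05 was mistyped. The margin feeds no threshold, test or stopping rule, and recruitment, analysis and the importance rule stay as they are. All of that stands, and it limits the point to a reporting error. It does not remove the error, because the sentence is the sole basis given for the sample size and nothing elsewhere in the article corrects it.

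Three stronger readings are tempting, and the document does not support them:

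- **That the survey is a hundredfold too small.** This would follow only if 0.5% were the true target. The exact match at 5% points the other way.
- **That small differences between retention measures would be mistaken for real ones.** A reader might infer this from an overstated precision. The plan, however, ranks items by Likert means and sets no comparison of percentages between measures. A margin in percentage points does not carry over to means on a 7-point scale. The same respondents also rate every item, so differences between items are paired, and the margin of a single proportion would not settle them.
- **That the margin is also wrong for the stakeholder groups.** The article claims the margin for the total sample and never for a group. Results are to be reported by group, but no between-group inference is planned. The group sizes are not fixed either: the text speaks of equal representation and also of proportional quota sampling. About 128 per group is thus an assumption, and the lack of a per-group margin is not an error.

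**Conclusion.** The point holds for one figure in one sentence. A proportion of 50%, 95% confidence and a 0.5% margin require about 38,415 respondents. The planned 385 corresponds to a 5% margin and delivers ±4.99 percentage points. The only stated precision of the survey is overstated tenfold in the margin, which equals about a hundredfold in sample size.

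That 5% was intended is an inference from the exact match; the article does not say so. The ±4.99 points also rest on simple random sampling and on 385 complete responses. With quota sampling through mailing lists and social media, and possibly snowballing, the corrected margin is a nominal figure too. It describes a percentage in the whole sample, not a Likert mean.

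No result, decision rule or recruitment target depends on the wrong figure, so the harm is confined to a wrong published statement of precision.

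**What to change.** In Sampling and sample size, Quantitative phase, change the margin of error from 0.5% to 5% and add in brackets that this means ±5 percentage points. Keep 385 there and in the abstract.

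Add one sentence saying that the margin applies to a proportion in the whole sample and is nominal, because it assumes simple random sampling while respondents will be recruited by quota and possibly by snowballing.

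Optionally, since results will be shown by stakeholder group, add that if the three groups are filled equally (about 128 each) the nominal margin within a group is about ±8.7 percentage points, under the same caveat.

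The cost is a wording correction: no additional respondents and no change to the analysis. The stated precision becomes less favourable, but it then agrees with the sample size. Should the investigators in fact have meant 0.5%, the correction would not suffice, and the sample size would have to be justified afresh.

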## Data collection

### Qualitative phase

We will conduct in-depth semi-structured interviews following a piloted interview guide. A copy of the interview guide is provided in the supplementary appendix (S1 Appendix). The interviews will be conducted over Zoom (a videoconferencing platform with real-time messaging and content sharing). The interview time will be booked according to the participants’ preference and will last approximately one hour.

At the beginning of the session, the trained interviewers will cover the study’s purpose, consent, and ethical issues, and establish rapport with the interviewees.

All the interviews will be recorded and transcribed verbatim by using a transcription service. About 10% of the transcripts will be compared by two authors (NR, CG) to the data transcribed by the transcription service for congruence and inconsistencies. Interview data will be anonymized and stored on secure and password-protected servers at McMaster University.

### Quantitative phase

This survey will be designed according to expert recommendations for electronic surveys [33].The web-based quantitative survey for participants will be conducted on the Research Electronic Data Capture (REDCap) tool, a secure, web-based application hosted and stored on a secure server at McMaster University [34]. The survey will be piloted before deployment. Participants will be presented with an overview of the study, the study’s purpose, the privacy and confidentiality of their data, and the time required to complete the survey. Participants will be invited to complete a consent form. The survey will be a self-administered, structured questionnaire in English.

The survey will consist of three parts: demographic information, professional information and questions related to measures of retention in HIV care. The themes identified in the qualitative interviews will serve as the survey items on the measures of retention. The participants will rate them on a 7-point Likert scale [35].

To ensure an adequate response rate, email addresses will be updated, and at least two reminder emails will be sent to potential participants.

## Analysis

### Qualitative phase

We will conduct a qualitative content analysis [36]. Transcriptions will be analyzed using content analysis techniques supported NVivo 10.

Both deductive and inductive content analysis procedures will be used in the following steps: (1) the initial coding framework for the deductive analysis will be informed by definitions of retention identified in our previous work [37]; inductive codes will be derived from the data by iterative readings of the interview transcripts. Similar codes will be put into categories according to their similarities and differences. The responses along with the number of participants in each category will be counted. The various categories will be organized in a table to create a visual and contextual interpretation [27].

After every seven to eight interviews, the two coders will meet to compare categories and arrive at an agreed-upon set of categories. Disagreement will be resolved by discussion to improve reliability between the two coders.

### Quantitative phase

We will compute the mean (standard deviation) or frequency (percent) based on the survey responses as appropriate for the data.

To determine the level of importance that participants allocate to each item we will compute the mean (SD) or median (quartiles). Only items with a mean of 4 or more out of seven will be considered as important. The mean will inform us which approaches to measuring retention are preferred by the participants. Results will be aggregated by stakeholder groups.

The results will be analyzed using IBM SPSS statistical software [38]. An outline of the study is shown in Fig 1.

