### Quantitative research questions

What components used to define retention are most important to HIV care stakeholders in terms of ease to use, recording, and comparison across different settings, jurisdictions, and studies?

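### Preference between retention measures is read from item means, with nothing to show whether close items differ by more than sampling error

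*Protocol article*

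**What the plan says.** The question under Quantitative research questions is comparative: "What components used to define retention are most important to HIV care stakeholders". The survey turns the interview themes into items, and "The participants will rate them on a 7-point Likert scale" (Data collection, Quantitative phase). I read this as every respondent rating every item.

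The Quantitative phase of the Analysis section sets out three things:

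- **Summary:** "To determine the level of importance that participants allocate to each item we will compute the mean (SD) or median (quartiles".
- **Cut-off:** "Only items with a mean of 4 or more out of seven will be considered as important".
- **Preference:** "The mean will inform us which approaches to measuring retention are preferred by the participants".

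Results are also to be given by stakeholder group. The sampling section plans for equal groups: "We will divide the sample into our pre-defined three strata (policy, health research, and practice) so every HIV stakeholder group is equally represented". No interval, paired comparison or rule for near-ties is named.

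**The concern.** Calling one approach preferred to another is a statement about a difference between items. The article rests that statement on separate point estimates. An SD or a pair of quartiles tells the reader how much people disagree about one item. It does not tell the reader how precisely the gap between two items is known.

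A reader of the results cannot repair this. A standard error for each mean follows from its SD and the number of respondents. The interval for a difference between two items rated by the same people also needs the correlation between their ratings, which the planned summaries do not supply.

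The survey results go into the joint displays and meta-inferences described under Data integration, and from there into the consensus framework. The Study design section says the survey will extend the interview findings to a larger sample, so sampling error bears on that use. If several items score closely, an apparent favourite, or an apparent disagreement between stakeholder groups about the favourite, may be chance.

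**Working it through.** **1. Sample size.** "We will obtain a pre-determined sample population of 385 based on the formula for proportions for a survey". For a proportion of 50% at 95% confidence, n = 1.96² × 0.25 / d². With d = 0.05 this gives 384.15, rounded up to 385. The margin as printed ("estimate a population proportion of 50% with a 95% level of confidence and a 0.5% margin of error") would need 38,415. That mismatch is a separate matter; 385 is used below. Either way, 385 was set for the precision of a proportion, not for differences between item means.

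**2. Inputs.** From the article: n = 385 overall, and 385 / 3 ≈ 128 per stakeholder group. Assumed, because the article gives neither: SD of an item rating 1.5 (range 1 to 2), and correlation r between two items within respondents 0.3 to 0.5 (range 0 to 0.7).

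**3. Precision of a difference between two items.** The 95% half-width is 1.96 × SD × √(2(1 − r)/n). With SD 1.5:

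- n = 385, r = 0.5: 1.96 × 1.5 × √(1/385) = 0.150
- n = 385, r = 0.3: 1.96 × 1.5 × √(1.4/385) = 0.177
- n = 385, pairing ignored (r = 0): 1.96 × 1.5 × √(2/385) = 0.212
- n = 128, r = 0.5: 1.96 × 1.5 × √(1/128) = 0.260
- n = 128, r = 0.3: 1.96 × 1.5 × √(1.4/128) = 0.307
- n = 128, pairing ignored: 1.96 × 1.5 × √(2/128) = 0.367

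The half-width is proportional to the SD. Over the whole assumed range (SD 1 to 2, r 0 to 0.7) it runs from 0.08 to 0.28 at n = 385 and from 0.13 to 0.49 at n = 128.

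**4. Chance that two items appear in the wrong order.** For a true gap δ this is Φ(−δ / (SD × √(2(1 − r)/n))). With SD 1.5:

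| True gap | n | r = 0.5 | r = 0.3 |
|---|---|---|---|
| 0.1 | 385 | 9.5% | 13.4% |
| 0.1 | 128 | 22.5% | 26.2% |
| 0.2 | 385 | 0.4% | 1.4% |
| 0.2 | 128 | 6.6% | 10.1% |

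**5. Spread produced by chance alone.** If ten items had the same true mean (SD 1.5, r = 0.5), simulation puts the average gap between the highest and lowest observed means at about 0.17 points with 385 respondents and 0.29 with 128. The number of items is also an assumption, since the items do not exist until the interviews are analysed.

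**The case against.** The strongest reply is that this is a condensed article. Confidence intervals and item comparisons are commonly left to a fuller protocol or analysis plan, so their absence alone would be no finding. That is right as far as it goes. The article is not silent, however: it states that the mean shows which approaches are preferred, and that rule is what needs tying to precision.

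A second reply is that the consequences are limited. The zone of uncertainty is a few tenths of a point on a seven-point scale, the one explicit decision rule is the per-item cut-off of 4, which does not depend on order, and the abstract's Limitations paragraph says a Delphi process will follow. All of this stands and limits the weight of the point.

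Three stronger readings are tempting and should not be made:

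- **That items will be ranked.** The article announces no ranking and no choice of a winner. An order is only something a reader could infer from the words about preference and importance.
- **That an SD is the only companion to the mean.** Median with quartiles is offered as an alternative summary.
- **That people who rate everything high or low distort the order.** With complete ratings such a person shifts every item mean equally, so the order is unchanged. The mean within-respondent difference equals the difference of the raw means; pairing changes the width of the interval, not the order.

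**Conclusion.** The point holds in a limited form. The article lets point-estimate means decide which approaches are preferred, and the summaries it names cannot show whether close items differ beyond sampling error.

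Under an assumed SD of 1.5 and correlation of 0.3 to 0.5, observed gaps smaller than about 0.15 to 0.18 points overall, or 0.26 to 0.31 points within a stakeholder group, do not separate two items at the 95% level. The group results are the more exposed. Items that differ by clearly more than this are unaffected, so the point matters only if the survey yields items that score closely. Whether it will cannot be known before the items exist.

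**What to change.** In the Quantitative phase of the Analysis section, add the following, both overall and by stakeholder group:

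- each item mean with a 95% confidence interval;
- the within-respondent difference of each item from the top-rated item, with a 95% interval (paired, or by bootstrap over respondents);
- a statement that items whose interval includes zero will be described as not distinguishable from the top item.

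Describe the intervals as model-based, because respondents are volunteers recruited by quota, possibly with snowballing. Say also whether the intervals allow for several comparisons and for the top item being picked from the same data. Step 5 of the working shows why: among ten equal items the average highest-to-lowest gap (0.17) already exceeds the half-width for a single pair (0.15).

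The cost is a few lines of analysis, with no new data and no change to the survey. The downside is that some items will be reported as tied, which is the honest result when they are.
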